##### Demographic and Clinical Characteristics

At baseline, participants answer questions regarding their biological sex, identified gender, age, ethnicity, education level, (potential) custody of children, marital and relationship status, sexual orientation, living situation, religion, employment, net income, income source(s), and the number of prior therapies received for which complaints, and within which theoretical framework. Any DSM classifications the participant has been diagnosed with at intake by the participating institution are retrieved from their electronic patient file.

##### Childhood Trauma Questionnaire – Short Form (CTQ-SF)

The Childhood Trauma Questionnaire – Short Form (CTQ-SF) employs 25 items to assess childhood trauma and distinguish between emotional neglect, physical neglect, emotional abuse, physical abuse and sexual abuse. Items are scored on a 5-point Likert scale, ranging from 1 (“Never true”) to 5 (“Very often true”) [87]. Internal consistency is found to be acceptable in a Dutch sample (*α *= 0.63–0.95) [88] and in a sample diagnosed with personality disorders (*α* = 0.81–0.91) [89]. The scale shows good factorial and convergent validity [88, 89].

##### PTSD Checklist for DSM-5 (PCL-5)

The post-traumatic stress disorder (PTSD) Checklist for DSM-5 (PCL-5) aims to screen for post-traumatic stress disorder using 20 items that correspond to the DSM-5 criteria [90]. Likewise, the four subscales of the instrument correspond to the DSM-5 clusters B through E for PTSD. The respondent rates the extent to which they suffer from a symptom using a 5-point Likert scale, ranging from 0 (“Not at all”) to 5 (“Extremely”). The instrument possesses good to excellent internal consistency (total scale *α* = 0.96, subscales *α* = 0.83–0.91) and satisfactory convergent/divergent validity [91].

##### Autism Spectrum Quotient (AQ-5)

The Autism Spectrum Quotient (AQ-5) is a very brief (5-item) screener, which has been derived from the AQ-10 [92] as a more psychometrically sound adaptation [93]. The AQ-5 measures social communication deficits, corresponding to Criterion A of the ASD diagnosis. The scale has acceptable internal consistency (*α* = 0.75) and convergent validity.

##### The Motivation to Engage Subscale of the Treatment Motivation Scales for Forensic Outpatient Treatment (TMS-F)

The Motivation to Engage (MET) subscale consists of 16 items and originates from the Treatment Motivation Scales for Forensic Outpatient Treatment (TMS-F). The MET subscale measures the participant’s commitment and readiness necessary for treatment to be successful [94]. Drieschner and Boomsma [94, 95] found the subscale possesses good internal consistency (*α* = 0.88) and adequate predictive and convergent validity.

##### Self-Reflection and Insight Scale (SRIS)

The Self-Reflection and Insight Scale (SRIS) uses 20 items to measure both inspection and evaluation (self-reflection; 12 items) and clarity of understanding (insight; 8 items) of one’s thoughts, feelings, and behaviour. Grant et al. [96] found good internal consistency (SRIS-SR *α* = 0.91; SRIS-IN *α* = 0.87), test-retest reliability (SRIS-SR *r* = 0.77; SRIS-IN *r* = 0.78), and convergent validity.

##### Locus of Control Scale (I-E)

The Locus of Control scale (I-E) assesses whether the locus of control is more internal or external, meaning to what extent a respondent perceives they can personally influence outcomes of events. The scale covers 10 items using a 5-point Likert scale [97]. Kamphuis and Emmelkamp [98] reported questionable but acceptable internal consistency (*α* = 0.66), while Sanderman [97] demonstrated adequate construct validity.

##### Mental Health Continuum – Short Form (MHC-SF)

The Mental Health Continuum – Short Form (MHC-SF) was developed by Keyes [99] to measure (hedonic and eudaimonic) well-being, which can be seen as a separate, but related, dimension to mental “ill-being” [100, 101]. The questionnaire contains 14 items divided into three dimensions: emotional well-being (EWB; 3 items), psychological well-being (PWB; 6 items), and social well-being (SWB; 5 items). Items can be answered using a Likert scale ranging from 0 (“Never”) to 5 (“Every day”). Validation of the instrument in a psychiatric sample confirmed the three-factor structure and revealed good internal consistency (total *α* = 0.92; EWB *α* = 0.88; PWB *α* = 0.85, SWB *α* = 0.77) [100].

##### Social problems list (IAPT)

Seventeen areas of social problems, such as unemployment and social isolation, are logged using yes/no items of the Social Problems list derived from the Improving Access to Psychological Therapies (IAPT) program [102]. An 18^th^ item provides the opportunity to log additional social problems not covered by the seventeen areas previously inquired. No prior psychometric validation has been executed.

##### Multidimensional Scale of Perceived Social Support (MSPSS)

The Multidimensional Scale of Perceived Social Support (MSPSS) questionnaire measures the perceived social support from family, friends, and a significant other [103, 104]. The 12 items are answered using a 7-point Likert scale ranging from “Very strongly disagree” to “Very strongly agree”. For the Dutch translation, Pedersen et al. [105] found the questionnaire to have excellent internal consistency (*α* = 0.94) and construct validity.

##### Stigma of Immutability Scale

For their multicentre RCT, Wibbelink et al. [86] developed a scale to assess the extent to which people believe their (borderline) personality disorder is resistant to treatment. The scale uses 7-point Likert scales to answer 5 items. No prior psychometric validation has been executed. Composite scores will be computed for each factor revealed by an exploratory factor analysis applied to the 5 item scores.

##### Dutch Version of the National Adult Reading Test (DART)

The Dutch version of the National Adult Reading Test (DART; [Nederlandse Leestest voor Volwassenen]; NLV) can be used to estimate (verbal) intelligence through assessment of the pronunciation of 50 words with irregular spelling [106]. The test has high internal consistency (*α* = 0.90) [107], inter-rater (*r* = 0.98) and retest reliability (*r* = 0.98) [108], as well as good criterion validity [109].

##### Questionnaire of Epistemic Trust (QET)

By administering the 24-item Questionnaire of Epistemic Trust (QET), insight is gained into a person’s developmental capacity to accept information as authentic, trustworthy, generalizable, and relevant to the self [110]. Items are answered using a 5-point Likert scale ranging from 1 (“Totally agree”) to 5 (“Totally disagree”). The instrument sheds light on four factors referring to hypervigilance, curiosity/openness, expectation of help, and openness to help. The QET has good to excellent internal consistency (total score *α* = 0.91, subscales *α* = 0.80–0.90), while also possessing satisfactory convergent/divergent validity [110].

##### Personality Inventory for DSM-5 – Short Form (PID-5-SF)

The Personality Inventory for DSM-5 – Short Form (PID-5-SF) assesses pathological personality traits across five domains and 25 facets [111–113]. A total of 100 items is answered on a 4-point scale ranging from 0 (“Very false”) to 3 (“Very true”) [111]. The measure has satisfactory construct and criterion validity, as well as good internal consistency on both the domain level (*α* = 0.89–0.91) and the facet level (*α* = 0.74–0.88) [113].

#### Plans to Promote Participant Retention and Complete Follow-Up {25b}

Participant retention is promoted through multiple strategies aimed at a personalised approach that minimises burdens and maximises accessibility [114, 115]. Whenever possible, existing data is reused to avoid redundant assessments. For example, STiP-5.1 interviews conducted during regular intake are repurposed for eligibility assessment and baseline measurements. Routine outcome monitoring (ROM) is adapted to prevent overlap with study instruments and again supplemented with SIPP-SF and BSI results at designated time points to facilitate usage during treatment trajectories. Before each assessment, research staff call participants to discuss their availability and preferred mode of completion (online or in-person), ensuring a participant-centred approach. Online assessment is set as the default to enhance convenience. Furthermore, participants receive a total reimbursement of €50, distributed across T1 (€15), T4 (€20), and T6 (€15). If a participant considers dropping out, research staff will encourage continued participation by offering a reduced test battery focused on collecting the primary outcomes at T4 and T6. The extent of this set depends on the participant’s willingness.

### Data Management {26}

All study data is centrally managed and securely stored for the duration of the trial in CASTOR EDC and for 15 years after trial completion. All data in CASTOR EDC is pseudonymised and stored on EU servers based in the Netherlands [116]. Hosting is NEN7510 compliant. Multi-factor authentication for research staff is enforced. Indefinite long-term storage on secured servers is facilitated by Tilburg University through TiU Dataverse, which is based on the Harvard University Dataverse repository.

Regarding data entry, included participants receive a study ID generated by CASTOR EDC. In all data files and during statistical analysis, participants are identified through their study ID, which can only be linked to personal data through a linking file (see *Confidentiality {33}*). All interview scores and data from electronic patient file records are entered manually by research assistants, while questionnaire responses are automatically captured during administration to participants in CASTOR EDC. When possible, data entry is checked and validated for a random case sample of entered STiP-5.1 and DART scores. Missing data during entry of questionnaires is prevented by CASTOR EDC through enforced item-based validation. Completed questionnaire packages are locked and cannot be altered. Only the junior researchers and the data manager are permitted to export data. Only the necessary research staff have access to exported data files. Exported data is checked, transformed and made anonymous on secured internal servers of Arkin GGZ, and stored and analysed on secured internal servers of Tilburg University. Data transformation is executed following automated scripts to guarantee transparency and replicability. In addition, CASTOR EDC produces a complete audit trail of all actions performed, e.g. fields updated and data exported.

### Statistical methods

#### Statistical methods for primary and secondary outcomes including harms {27a}

*Non-inferiority.* The primary research question is answered through longitudinal multilevel modelling of the short-term difference (T4; 18 months) between generalist (GIT-PD) and specialist treatment (MBT/ST) in improvement of personality functioning, following the intention-to-treat principle. Two separate multilevel mixed-effects models are used for the two primary outcomes, meaning both the STiP-5.1 at two time points and the LPFS-BF 2.0 at five time points. The model levels refer to the repeated measurements (level 1) of each individual (level 2) nested within treatment sites (level 3). Both models will be adjusted for the respective baseline outcome value, while random intercepts and slopes are modelled to account for the heterogeneous individual change trajectories over time. Furthermore, random intercepts and slopes are modelled on the treatment site level to account for heterogeneous change trajectories across sites. No further covariates will be added. Two-tailed significance levels are set at *α* = 0.05, while effect estimates are reported with corresponding 95% two-sided confidence intervals. If the required sample size is not achieved due to problems with enrolment and inclusion, all non-inferiority analyses are converted to a one-sided confidence interval approach in order to retain sufficient statistical power. In case of convergence issues, the model’s complexity will be reduced by 1) not modelling the random slope but only the random intercept at the third level of treatment site, 2) replacing treatment site with institution with regards to the third level along with the respective random intercepts and slopes, or 3) omitting the third level in the analysis altogether if necessary. Trial-level non-inferiority will be assessed using a fixed-sequence testing procedure [117], prioritising the clinician-rated LPF (STiP-5.1) due to its blinded assessment and superior capability of measuring latent PD severity [58, 59]. If non-inferiority is demonstrated on the STiP-5.1, the self-reported LPFS-BF 2.0 will be tested subsequently to provide additional supportive evidence, given its high sensitivity to change [60]. If non-inferiority is not demonstrated on the STiP-5.1, the LPFS-BF 2.0 will not be formally tested as a primary outcome, and non-inferiority cannot be concluded at the trial level. This hierarchical approach preserves statistical power while controlling the family-wise error rate across multiple endpoints and prioritising blinded assessment to minimise potential bias.

To answer the secondary research questions regarding long-term (T6; 30 months) non-inferiority of generalist (GIT-PD) versus specialist treatment (MBT/ST) in improving personality functioning, an identical intention-to-treat longitudinal multilevel model will be fit as for the primary outcome, while including all available repeated measures. This ultimately results in the inclusion of three and seven repeated measures for the STiP-5.1 and LPFS-BF 2.0, respectively. Likewise, to assess the short-term (T4; 18 months), as well as the long-term (T6; 30 months) non-inferiority of generalist (GIT-PD) versus specialist treatment (MBT/ST) in improving symptom severity and psychosocial functioning, the same intention-to-treat longitudinal multilevel model will be applied for each of the secondary study parameters (SIPP-SF, SCID-5-PQ, BSI, C-SSRS, WHODAS 2.0, EQ-5D-5 L, Q-LES-Q-SF). Likewise, for the short-term outcome, the five repeated measures (level 1) of each individual (level 2) are nested within treatment sites (level 3). Models are adjusted for the respective outcome’s baseline value, random intercepts, and slopes are modelled at the second and third level to account for heterogeneous individual and treatment site change trajectories over time, and two-tailed significance levels are set at *α* = 0.05, while effect estimates are reported with corresponding 95% two-sided confidence intervals. The non-inferiority margin is set at *d* = − 0.25. On top of that, all AEs and SAEs are descriptively reported for both treatment arms.

*Cost-effectiveness.* To assess the cost-effectiveness of treatments, we will conduct a comprehensive economic evaluation consisting of a cost-effectiveness analysis (CEA) and a cost-utility analysis (CUA). The analyses will be conducted and reported following [118], the CHEERS 2022 statement [119] and the ISPOR good research practices task force report on cost-effectiveness analysis alongside clinical trials II [120]. To evaluate the cost-effectiveness, improvement in LPF (as measured with the LPFS-BF 2.0 and STiP-5.1) is set off against costs incurred from the societal perspective. Treatment costs within the context of the participating mental health treatment centres are measured using patient file data (e.g. treatment minutes and type of therapist). Costs outside of the participating treatment centres are assessed with the TiC-P questionnaire. The TiC-P has a recall period of 3 months, which will be linearly extrapolated to complement the full intervals between time points. All cost estimates will be based on reference pricing as defined by Hakkaart-Van Roijen et al. [121].

For the CUA, health utilities are calculated using the Dutch tariff for the EQ-5D-5 L [122]. These utility scores will be used to calculate quality-adjusted life years (QALYs). QALYs gained between baseline measurements and the primary endpoint at 18 months after the start of treatment are the outcome variable for the CUA. This outcome variable is defined as the number of life years gained adjusted for quality of life. By projecting QALYs gained per condition as an operationalisation of utility, the cost-utility of the assigned intervention will be determined. In sum, we aim to execute the CEA and CUA from the societal perspective based on intention-to-treat analyses with an estimated time-horizon of 18 months after T0 for the economic evaluation on the primary endpoint.

For both the CEA and CUA, the incremental costs (electronic patient file data and TiC-P) and the incremental effects (change in LPF as measured with the LPFS-BF-2.0 and STiP-5.1 for the CEA; QALYs as measured with the EQ-5D-5 L for the CUA) will be used to calculate incremental cost-effectiveness ratios (ICER). The uncertainty and robustness of the ICER will be analysed using bootstrapping. Next, the bootstrapped ICER will be plotted on cost-effectiveness planes where the horizontal axis displays the difference in effectiveness and the vertical axis displays the difference in costs. Further, the ICER will be used to examine willingness-to-pay (WTP) levels and then will be plotted in cost-effectiveness acceptability curves, displaying the cost-effectiveness of the experimental condition compared to the active control condition. Hence, WTP analysis will be conducted to determine the incremental costs per incremental unit of effect (QALYs or change in LPF) gained compared to WTP thresholds. A fitting discount rate will be applied for outcomes and future costs in accordance with NICE guidelines [123] and Drummond et al. [118]. Uncertainty in results will be assessed using both bootstrapping and sensitivity analyses. Variability and heterogeneity analyses will be conducted. Potential subgroups based on patient characteristics will be part of exploratory analyses.

*Personalised Advantage Index*. In examining what treatment works better for whom, an algorithm will be built that predicts differential treatment responses regarding LPF between generalist and specialist treatment. The algorithm quantifies the magnitude by which either treatment is estimated to outperform the other on the participant level, using the Personalised Advantage Index (PAI). The PAI was initially developed by DeRubeis et al. [44], but recently Meinke et al. [124] revised the algorithm, addressing key analytical issues in the traditional approach. As a result, this Advanced PAI approach introduced less risk of bias and prevented data leakage, thus providing more precise estimates while minimising the risk of overestimating model performance. Following Meinke et al.’s [124] guidance, PAI analyses will be conducted using their open-source code. This means a 5-fold cross-validation with 100 iterations will be utilised, covering not only the data preprocessing steps in terms of candidate predictor exclusion, imputation, and selection but also training, testing, and evaluating the performance of the models. More specifically, candidate predictors will be excluded if more than 30% of values are missing, while imputing missing values for the remaining candidate predictors. Herein, the mode will be used for categorical and binary variables, while multivariate imputation by chained equations (MICE) is going to be used for numerical variables. Furthermore, predictors lacking variance and binary predictors with 90% of participants or more in either category will be excluded. Multicollinearity between candidate predictors is operationalised as Pearson correlation (numerical variables) or Jaccard similarity (binary variables) of  > 0.75. Either of two similar candidate predictors should be removed by excluding the variable with the highest mean correlation/similarity with the remaining predictors. Candidate predictor exclusion will be repeated until no correlation/similarity of  > 0.75 is observed.

Subsequently, distinct prediction models are to be fitted for the generalist and specialist treatment. First, predictors will be selected using Elastic Net regression, which is a supervised machine-learning method that combines the penalised linear Lasso and Ridge regressions to identify a parsimonious and stable subset of predictors. Then, Ridge regression will be used to fit the final prediction models using the selected predictors per treatment. For the participants in the test-fold of the 5-fold cross-validation, the resulting prediction models will be used to calculate a ‘factual’ prediction for the treatment actually received and a ‘counterfactual’ prediction for the treatment not actually received. To quantify the performance of the prediction models for both treatments, the outcome of the factual prediction will be compared to the actual LPF at post-treatment in terms of the mean absolute error (MAE), the root mean square error (RMSE), and the correlation.

The PAI scores are then derived from subtracting the counterfactual prediction from the factual prediction to discern whether a participant received their optimal or non-optimal treatment. Negative and positive PAI scores refer to having received the optimal and nonoptimal treatment, respectively. The PAIs utility in guiding treatment selection will be evaluated through comparing LPF at post-treatment for participants having received their optimal versus nonoptimal treatment using an independent one-sided t-test. Additionally, Cohen’s *d* will be computed for the mean difference. As per customary practice in PAI analyses, this evaluation should be repeated for the 50% of participants with the largest absolute PAI scores to determine utility for those with the strongest predictions. The Advanced PAI approach will be performed for both the clinician-rated (STiP-5.1) and the self-reported LPF (LPFS-BF 2.0).

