### Sample size {19}

The required sample size was determined using a computer simulation. Twenty-one thousand datasets with varying sample sizes were simulated for an RCT design with seven repeated measurements on a continuous outcome variable, where both interventions exhibit equal improvement over time. The outcome measures were assumed to follow a multivariate normal distribution in both groups, with a repeated measures correlation of 0.50 and a decrease of *d* = 0.30 in both groups across the seven repeated measurements. Each of these datasets was analysed using a longitudinal multilevel model (see *Statistical methods for primary and secondary outcomes, including harms {27a}).* Subsequently, in each dataset, it was tested whether generalist treatment is non-inferior to specialist treatment by examining whether the lower limit of the two-sided 95% confidence interval of the difference between treatments in improvement over time is greater than the non-inferiority limit of *d* = 0.25. It was found that with this design, 316 participants are necessary (158 per group) to test non-inferiority with a power of 0.80 and α = 0.025. To account for attrition, which we estimate at 11.7% for the primary endpoint (T4) based on a similar study [19], the complete sample needs to consist of (316/0.883 = 357.87) 358 participants. This comes down to 179 participants per treatment condition.

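### The one-sided interval triggered by a recruitment shortfall either changes nothing or, on its natural reading, raises the false non-inferiority rate at the margin from 2.5% to 5%

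*Protocol article*

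**What the plan says.** Three statements in the Protocol article bear on this point.

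- **Sample size {19}.** The criterion applied to each simulated dataset is "the lower limit of the two-sided 95% confidence interval of the difference between treatments in improvement over time", set against the margin. The result is that "316 participants are necessary (158 per group) to test non-inferiority with a power of 0.80 and α = 0.025", raised to 358 for 11.7% attrition.
- **Statistical methods {27a}, main rule.** "Two-tailed significance levels are set at *α* = 0.05, while effect estimates are reported with corresponding 95% two-sided confidence intervals".
- **Statistical methods {27a}, fallback.** "If the required sample size is not achieved due to problems with enrolment and inclusion", then "all non-inferiority analyses are converted to a one-sided confidence interval approach in order to retain sufficient statistical power". The article gives no confidence level for this interval, no size of shortfall that activates it, and no reason other than power.

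The same section sets a fixed sequence, STiP-5.1 first and LPFS-BF 2.0 second, and says of it: "This hierarchical approach preserves statistical power while controlling the family-wise error rate across multiple endpoints".

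**The concern.** A non-inferiority decision uses only the lower confidence limit. The planned two-sided 95% interval is therefore already a one-sided test at 0.025, and the sample-size section says as much by giving α = 0.025. Calling the interval one-sided adds no power unless the confidence level also drops. The fallback is thus either empty or a relaxation of the error rate that depends on how many participants were enrolled.

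The margin of d = −0.25 equals the lower end of the advantage of psychotherapy over treatment as usual that the Primary objective cites (0.25 to 0.56). If that lower end is right, a true difference at the margin means that generalist care has lost the whole advantage. The false non-inferiority rate is the chance of missing this, and the trial is meant to inform how specialist care is allocated. The fallback covers every non-inferiority analysis, so it also reaches the secondary outcomes at 18 and 30 months.

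**Working it through.** **Inputs from the article:** margin 0.25 SD; true difference 0; one-sided α 0.025; power 0.80; 158 per group; attrition 11.7%; seven measurements with correlation 0.50; 1:1 allocation. **Assumptions made here:** normal approximation, compound symmetry, equally spaced measurements.

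**1. The plan's own figure.** Over seven equally spaced measurements, the modelled total change has SD √(0.50/0.7778) = 0.802. Then n per group = 2 × 0.802² × (1.960 + 0.842)² / 0.25² ≈ 162, or 324 in total, against the stated 158 and 316 (2.5% apart). Using the actual visit months gives 151 per group. Attrition: 316/0.883 = 357.87, so 358, as stated. With seven equally spaced measurements, one-sided 0.05 would need only 128 per group. The stated figure therefore fits the 0.025 that the article gives.

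**2. Error rate at the margin.** With a true difference of −0.25, the chance that the lower limit exceeds −0.25 is 1 − Φ(z).

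| Bound | z | False non-inferiority |
|---|---|---|
| Two-sided 95%, lower limit | 1.960 | 0.025 |
| One-sided 97.5% | 1.960 | 0.025 |
| One-sided 95% | 1.645 | 0.050 |

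Two million normal draws per sample size gave 0.0249 and 0.0500 at 158 per group, 0.0251 and 0.0502 at 125, and 0.0249 and 0.0500 at 100 (two-sided 95% and one-sided 95% respectively). The doubling does not depend on N or on the SD.

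**3. What the switch buys.** Calibrate the standard error so that 158 per group gives 0.80 power: 0.25/SE = 1.960 + 0.842 = 2.802. Power at n per group is Φ(2.802 × √(n/158) − z). At n = 140, 2.802 × √(140/158) = 2.637, so:

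- planned rule: Φ(2.637 − 1.960) = 0.751
- one-sided 95%: Φ(2.637 − 1.645) = 0.839

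| Evaluable | Planned rule | One-sided 95% |
|---|---|---|
| 316 | 0.80 | 0.876 |
| 300 | 0.78 | 0.86 |
| 280 | 0.75 | 0.84 |
| 250 | 0.70 | 0.80 |
| 200 | 0.61 | 0.72 |

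The ratio of sample sizes for equal power is (1.645 + 0.842)²/(1.960 + 0.842)² = 0.788, and 316 × 0.788 = 249. At 125 per group the observed d needed to pass loosens from −0.053 to −0.085.

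**4. The trigger.** No minimum shortfall is given, and the required size could mean 316 or 358. One participant short is enough as worded. Power just under target is then about 0.88 (0.876 at 158 per group, almost unchanged with one fewer), against 0.80 for a trial that met its target.

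**5. Limit of the power figures.** Step 3 rests on the seven-measurement simulation. The STiP-5.1 model that gates the conclusion uses two time points. As one variant, take a baseline-adjusted comparison with correlation 0.50 (SD √0.75 = 0.866). At 140 per group, 0.25/(0.866 × √(2/140)) = 2.415, so power is Φ(2.415 − 1.960) ≈ 0.68 under the planned rule and Φ(2.415 − 1.645) ≈ 0.78 after the switch. The levels are lower, but the error rates in step 2 are the same.

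**The case against.** The best defence is that the rule is declared in advance and triggered by enrolment, not by outcome data. No interim analysis is planned, and the analysts work with pseudonymised arms. This stands, and it bounds the harm: given a shortfall, the rate at the margin is 5% and no higher, and averaged over shortfall and no shortfall it lies between 2.5% and 5%. It does not explain why the standard of evidence should depend on recruitment.

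It can also be said that one-sided 5% may be a defensible level. If so, it should be justified and fixed for every enrolment scenario. The article chose 0.025 and gives no ground but power for leaving it.

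A reader might infer more than the article supports in four ways:

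- **That 5% is stated.** It is not. The article is a condensed account, and the fuller protocol it refers to is not at hand and may give a level.
- **That family-wise error control fails.** It does not. A fixed sequence controls error at whatever level each test uses. After the switch the primary family would be held at one-sided 5% instead of 2.5%.
- **That the sponsor could profit by stopping early.** The trigger is limited to enrolment and inclusion problems, and the Recruitment section sets monthly forecasts, monitoring and corrective action. Nothing suggests strategic under-recruitment.
- **That about 282 randomised (358 × 0.788) would be fully powered after the switch.** This follows only from the seven-measurement calibration. Under the two-time-point variant, 0.80 power at one-sided 0.05 needs about 149 per group, or 298 evaluable.

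**Conclusion.** The concern holds as a two-way statement: the fallback is either without effect or, read so that it does what it says it is for, raises the false non-inferiority rate at the margin from 2.5% to 5%. That contradicts the article's own basis, "to test non-inferiority with a power of 0.80 and α = 0.025". The 5% is inferred from the stated purpose. The doubling holds per test at a true difference equal to the margin and does not depend on sample size. The power figures are illustrative and rest on the article's seven-measurement simulation. The undefined trigger is a defect in its own right, because a trial that narrowly misses its target would pass more easily than one that meets it. Since the sentence governs the primary conclusion, it should be corrected before analysis.

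**What to change.** Delete the fallback sentence. State instead that non-inferiority is judged by the lower limit of the two-sided 95% confidence interval (one-sided α 0.025) whatever number is enrolled, and that a shortfall is reported as reduced power and a wider interval. A one-sided 95% bound may be shown if it is labelled descriptive and carries no decision.

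The edit is one sentence. The real cost is that power falls if recruitment does, along the planned-rule column above: on that calibration, 0.75 with 280 evaluable and 0.61 with 200. That loss reflects the smaller sample, and the report should show it.
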